### Setting

Patients will be recruited in 9 participating centers across Flanders, that is, the University Hospitals of Leuven (UZ [Universitair Ziekenhuis] Leuven), and the general hospitals of Pelt (Noorderhart Mariaziekenhuis), Mol (Heilig Hartziekenhuis), Herentals (AZ [Algemeen Ziekenhuis (general hospital)] Herentals), Turnhout (AZ Turnhout), Izegem (Sint-Jozefskliniek), Halle (AZ Sint-Maria Halle), Tienen (RZ Heilig Hart Tienen), and Malle (AZ Voorkempen). The expected recruitment period, from First Patient In to Last Patient In, is 11 months, starting March 10, 2025. The total inclusion period from First Patient In to Last Patient Out is expected to take approximately 18 months. The total period of intervention plus follow-up for every single patient depends on the LOS, that is, until 200 days after discharge from the hospital, to collect the secondary end point parameters: in-hospital mortality, 3-month posthospitalization mortality, LOS, and 3-month readmission rate. Patients who are still in the hospital when the end of the recruitment period is reached (estimated February 2026, when the needed sample size was reached) will be excluded. For comparison, in a recent retrospective study in UZ Leuven, involving 21,999 patients with pneumonia, pyelonephritis, infections associated with heart, kidney, liver, or lung transplantation, appendectomy, coronary artery bypass grafting, and total knee or hip replacement, the average LOS in UZ Leuven for patients with BLAL was 21 days (SD 39) [21].

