For the intra- and intercluster correlation (ICC), literature indicates a moderate ICC of 0.059 for antibiotic prescription behavior [35,36]. This estimate seems appropriate as moderate differences in antibiotic prescription behavior are expected within and between different physicians at participating sites, which mostly follow the IGGI guidelines, however, with some internal adjustments. Indeed, the most recent point prevalence survey of antimicrobial use and health care–associated infections in Belgian acute care hospitals (results of the global point prevalence survey and European Center for Disease Prevention and Control point prevalence survey) reports 77% compliance with IGGI guidelines [37]. Additionally, 3 participating sites are part of the same Hospital Outbreak Support Team network, that is, Heilig Hartziekenhuis Mol, AZ Turnhout, and AZ Herentals in the Hospital Outbreak Support Team Network Kempen, which has the specific goal to align antimicrobial stewardship. All centers use the same EPR (CWS). The major difference would be expected between UZ Leuven, as an academic hospital, and the other participating sites, as regional hospitals. The AFC is currently only available in the CWS EPR system, and therefore, we were unable to include other academic centers as well. A sensitivity analysis of academic vs regional hospitals will be performed.

Considering the number of hospitalizations per year in each center and a prevalence of 6% of BLALs [8], we expect an inclusion rate of 3285 participants.

Sample size and power calculations were carried out according to the methods described by Hemming et al [38], using the Shiny CRT Calculator [39]. Based on the design given in Figure 1, assuming a discrete time decay (allowing correlations between periods to decay with each period), a within-period ICC of 0.059 and an autocorrelation (ratio of between-period and within-period ICC) of 0.6, this study will have 80% power to detect a statistically significant difference between control and intervention using a 2-sided significance level of 5%, assuming 4.6% and 9.9% of patients to have the primary end point in the control and intervention group, respectively. This sample size calculation is based on patient-level appropriate prescribing proportions and is considered a conservative approximation for the cumulative window-based primary end point.

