### Statistical Analysis

The primary endpoint is cumulative guideline-concordant use of first-line and/or narrow-spectrum beta-lactam antibiotics according to IGGI-based local guidelines, assessed across predefined assessment windows up to day 100 (days 1, 30, and 100). Within each window, guideline concordance is scored at the patient level in an any or ever manner as 1 if at least one in-hospital systemic antibiotic course is guideline-concordant and 0 if otherwise. If multiple courses occur within a window, the window is considered concordant if any course meets guideline criteria. This any or ever approach was chosen in line with the quality-improvement objective of the AFC intervention, capturing whether appropriate first-line therapy was achieved within a care window while limiting instability due to multiple within-episode treatment changes. Windows without in-hospital systemic antibiotic administration are considered not applicable (“no opportunity”) and are excluded from the denominator.

For each patient, a cumulative weighted guideline-concordance score is calculated at day 100 as the proportion of applicable windows with guideline-concordant therapy (*sᵢ/nᵢ*). The primary comparison between intervention (AFC) and control will use a binomial generalized linear mixed-effects model with logit link, modeling *sᵢ* out of *nᵢ*, including fixed effects for study phase and period, and a random intercept for hospital to account for clustering in the crossover design. A prespecified adjusted model will additionally include age, sex, and the Charlson comorbidity index. Patients without any applicable windows will be excluded from this analysis and reported separately. The primary estimand targets the period during which the AFC is expected to plausibly influence prescribing through contemporaneous decision support and short-term label adjustment.

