Secondary endpoints include guideline-concordant beta-lactam use at each individual assessment window (including day 200), delabeling or refinement rate, beta-lactam tolerance, antibiotic switching, ICU admission, readmission, resistant organism outcomes, LOS, mortality, and cost outcomes. Outcomes at day 200 are analyzed as secondary durability measures, as longer-term prescribing may be influenced by label reappearance or documentation changes unrelated to the index intervention. Secondary endpoints will be analyzed using hierarchical mixed-effects models appropriate to outcome type (binary, continuous, or time-to-event), with fixed effects for study phase and period and clustering by hospital. Process evaluation outcomes will be analyzed descriptively.

Predefined subgroup analyses will assess potential effect modification by including phase-by-subgroup interaction terms in the primary model. Subgroups of interest are BLAL type (penicillin vs other labels), reported reaction severity category, time since label registration, infection type (prophylaxis vs therapeutic indication), ICU admission status, and hospital type (academic vs regional). Subgroup analyses will focus on the primary endpoint and are considered exploratory and hypothesis-generating. 

Moreover, because the AFC is expected to influence prescribing primarily through label delabeling or refinement, we will perform an exploratory implementation analysis within the AFC phase. Patients will be classified as with implementation if the BLAL was delabeled or refined after the AFC recommendation, and as not with implementation if otherwise. The cumulative primary endpoint (*sᵢ/nᵢ* up to day 100) will be summarized by implementation status; any between-group comparisons will be considered descriptive and interpreted cautiously, as implementation is a postallocation process measure and may be confounded.

No formal adjustment for multiplicity will be applied. Secondary and subgroup analyses will be interpreted with caution.

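### The predefined academic-versus-regional interaction sets one hospital against eight, so it cannot show effect modification by hospital type

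*Protocol article*

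**What the plan says.** The Setting section gives the number of sites: "Patients will be recruited in 9 participating centers across Flanders". Sample Size Determination divides them into "UZ Leuven, as an academic hospital, and the other participating sites, as regional hospitals", and explains that the AFC runs in one EPR system only, so "we were unable to include other academic centers as well". The same paragraph adds: "A sensitivity analysis of academic vs regional hospitals will be performed". It does not say what form that analysis takes.

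In Statistical Analysis, effect modification is to be assessed by "including phase-by-subgroup interaction terms in the primary model". The list of six subgroups ends with "infection type (prophylaxis vs therapeutic indication), ICU admission status, and hospital type (academic vs regional", so hospital type is the last of them. The primary model is a binomial mixed model "including fixed effects for study phase and period, and a random intercept for hospital to account for clustering in the crossover design". It has no hospital-by-period or hospital-by-phase term. Subgroup analyses are labelled exploratory. Alternative covariance structures and GEE with robust standard errors appear as sensitivity analyses.

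**The concern.** Hospital type is a property of hospitals, so the replicates for this contrast are hospitals, and the academic side has one. Its academic status cannot be separated from everything else particular to it: its identity, its place in the non-randomised sequence scheme and the calendar periods in which it was observed. The other listed subgroups can vary between patients within a hospital and do not share this feature.

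The primary model builds the interaction's standard error from variation between patients plus a constant hospital level. The power calculation, however, assumes that hospitals also fluctuate from period to period. The reported p-value would be too small for that reason as well.

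At stake is how one exploratory result is read. A positive interaction could be reported as evidence that the tool works differently in academic hospitals, and a null one as evidence that it works alike in both types. Neither would follow.

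**Working it through.** **Inputs from the protocol article**
- Nine hospitals, one academic (Setting; Sample Size Determination).
- Within-period ICC 0.059; autocorrelation 0.6 per period (Sample Size Determination).
- 3285 participants, about 30% on antibiotics: 3285 × 0.30 ≈ 985. Patients without an applicable window leave the primary analysis (Missing Data).
- 4.6% and 9.9% of all patients; divided by 0.30, this is 15.3% and 33.0% of recipients, a difference of 0.177.
- Sequences of four 3-week periods, so 12 weeks per pass (Design). Recruitment of 11 months, about 48 weeks (Setting), leaves room for about four passes at a site that recruits throughout.

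**Assumptions.** One, two or four passes (Figure 1 is not shown); academic share of patients from 1/9 to 50%; equal regional hospitals; one binary outcome per patient; linear scale; normal test; no true interaction.

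**The plan's own figure.** None is given for this interaction. For the main comparison (nine equal hospitals, 3285 patients), power comes to 55%, 84% and 97% with one, two and four passes. The stated 80% lies within that range, so without Figure 1 it can be neither confirmed nor contradicted.

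**Step 1: what the term estimates.** Write the AFC effect in hospital j as μ + γ·A_j + u_j, with A_j = 1 for the academic hospital and u_j the hospital's own deviation. Academic minus mean regional estimates γ + u_academic − mean(u_regional). With one hospital at A = 1, γ and u_academic appear only as a sum. No covariance structure separates them.

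**Step 2: standard error by hand (equal hospitals, four passes, period terms ignored).**
- Mean proportion (0.153 + 0.330)/2 = 0.242; variance v = 0.242 × 0.758 = 0.183.
- Hospital-period part: 0.059 × 0.183 = 0.0108. Patient part: 0.941 × 0.183 = 0.172.
- Each hospital has 985/9 = 109.4 recipients over eight alternating periods, two apart, so neighbours correlate 0.6² = 0.36. The period part is multiplied by f = [8 + 2·Σ(8−d)(−0.36)^d, d = 1..7]/16 = (8 − 3.85)/16 = 0.260.
- Variance of one hospital's phase contrast: 4 × 0.172/109.4 + 0.260 × 0.0108 = 0.0063 + 0.0028 = 0.0091.
- True interaction variance, one hospital against the mean of eight: 0.0091 × (1 + 1/8) = 0.01025; SE 0.1012.
- Reported by the random-intercept model: (4 × 0.183/109.4) × 1.125 = 0.0075; SE 0.0868.
- Type I error: 2[1 − Φ(1.96 × 0.0868/0.1012)] = 2[1 − Φ(1.68)] = 9.3%.
- The phase effect in the eight regional hospitals has the same ratio of reported to true SE, because both variances are divided by 8. Its type I error is therefore also 9.3%.

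**Step 3: the same calculation in matrix form, with period terms and an academic main effect.** Ranges cover academic shares of 1/9, 30% and 50%.

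| Passes | Reported SE | True SE | Type I error, interaction | Type I error, phase effect in regional hospitals |
|---|---|---|---|---|
| 1 | 0.075-0.096 | 0.156-0.166 | 26-34% | 18-26% |
| 2 | 0.075-0.096 | 0.117-0.131 | 15-21% | 10-15% |
| 4 | 0.075-0.096 | 0.096-0.112 | 9-12% | 7-9% |

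A logistic simulation of the same setting gives 17-24%, 11-15% and 8-10% for the interaction. Another run of the linear calculation gives 10-14% at four passes. Together these make the four-pass range about 8-14%.

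**Step 4: what a correct standard error could detect (four passes).** For 80% power: (1.96 + 0.84) × 0.096 = 0.27, up to 2.80 × 0.112 = 0.31. For an interaction as large as the whole planned effect, power is between Φ(0.177/0.112 − 1.96) = Φ(−0.38) = 35% and Φ(0.177/0.096 − 1.96) = Φ(−0.12) = 45%. Real variation in the AFC effect between hospitals would widen the true SE further and is not included.

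**The case against.** The strongest reply is that the inflated error is not about hospital type. It comes from leaving hospital-by-period variation out of the primary model, and with equal hospitals the phase effect is inflated just as much. This stands. The excess that belongs to hospital type appears only when the academic hospital is large: 12% against 7-8% at four passes with a share of 30-50%.

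The planned covariance alternatives could repair the standard error, and the term would then be a fair test of whether this hospital differs from the others. That stands in part. They are sensitivity analyses, robust standard errors are unreliable when one side of a contrast is a single cluster, and none of them supplies a second academic hospital.

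The protocol also calls the subgroup analyses exploratory and openly says that no other academic centre could join. This lowers the weight of the point. But the label covers all six subgroups alike, and nowhere is the reader told that this contrast rests on one hospital.

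Several stronger readings are tempting and not supported:
- That the term measures only chance. It would also pick up a genuine difference in AFC effect at that hospital.
- That error rates of 26-34% apply. Those need a single pass, whereas the recruitment period fits about four, though sites that join late would complete fewer.
- That rates on all 3285 patients apply (20-26% even at four passes). The primary analysis excludes patients without antibiotic exposure.
- That the protocol expects its largest difference in AFC effect here. The remark in Sample Size Determination concerns prescribing behaviour, and the hospital intercept absorbs differences in level.
- That the academic-versus-regional sensitivity analysis repeats the error. Its form is left open.

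**Conclusion.** The point holds, as a minor one. The interaction cannot answer the academic-versus-regional question, whatever the sample size, number of passes or covariance structure, because academic status and one hospital's identity coincide. This part rests on no assumption beyond the site list.

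The numerical part is conditional on the assumed number of passes and academic share. At four passes the nominal 5% test rejects in roughly 8-14% of trials with no true interaction, and more often with fewer passes. Much of that belongs to the primary model's covariance. With a correct standard error of about 0.10-0.11, only an interaction of about 0.27-0.31 has 80% power, which exceeds the planned effect of about 0.18. A null result is therefore uninformative.

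No primary conclusion depends on this analysis.

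**What to change.** - Remove hospital type from the phase-by-subgroup interaction tests.
- Define the academic-versus-regional sensitivity analysis as the AFC effect with the academic hospital left out (eight regional hospitals), shown beside the all-hospital estimate.
- Show each hospital's own phase contrast in a descriptive plot, with intervals that allow for hospital-by-period variation.
- State that effect modification by hospital type cannot be tested with one academic hospital.

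The statistical analysis plan is still to be finalised before database lock, so this can go in there. The cost is some wording, one extra model fit and the loss of one exploratory p-value.

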These concerns led to the emergence of invasive delabeling protocols for penicillin allergy labels in the United States and Australia [22,23]. Current approaches use risk stratification based on clinical history and direct challenges (ie, in-hospital, but without prior skin tests) with penicillins or alternative beta-lactams in identified low-risk patients [24,25]. The efforts demonstrate to be cost-effective [22] and impact antibiotic use, shifting more to first-line beta-lactams and narrow-spectrum penicillins [26]. However, a relevant fraction of readministrations was accompanied by a repeat hypersensitivity reaction (3.8%), of which a minority (<1%) were severe [26]. This illustrates the delicate balance between indirect harm through incorrect BLAL and repeat iatrogenicity through invasive delabeling protocols themselves.

An often forgotten step in the delabeling process that encompasses the lowest risk for repeat iatrogeny is noninvasive delabeling. Here, without skin or drug provocation testing, but solely by using patient questionnaires and information from tolerated antibiotic exposures, discordances in the EPR are exploited to the advantage of the patient [9,27-29]. Our group prospectively evaluated in an EU context a noninvasive delabeling protocol in adult internal medicine inpatients with a BLAL [30], combining (1) an allergy-oriented clinical history, (2) an EPR search to identify incorrect BLAL and/or uneventful re-exposures to beta-lactams, and (3) a systematic primary care physician and community pharmacist contact. Using this approach, 38% of BLALs could be delabeled, and another 27% could be refined, largely driven by EPR findings. In the next step, we optimized the EPR search by developing a semiautomated clinical decision support (CDS) tool, designed to identify those patients with documented re-exposure without allergic reaction. A proof-of-concept study, limited to penicillin allergy labels, demonstrated the feasibility and efficacy of this novel CDS tool, identifying nearly 10% of alleged penicillin-allergic patients and showing approximately sevenfold higher odds of delabeling after its introduction [31]. Importantly, the impact on prescription behavior and major clinical outcome parameters is unknown and would be the basis for broad roll-out. Therefore, we propose to perform the first multicenter study on noninvasive BLAL delabeling, using an EPR-embedded, semiautomatic, intelligent “Allergy Fact Checker (AFC)” CDS tool.

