### BLAL Adjustment (Intervention Group, if Applicable)

In the case of a correct or undetermined BLAL, no action will be taken. In case of an incorrect BLAL, a suggestion will be sent to the treating physicians in the EPR (“follow-up note”), to delabel (re-exposure to the culprit found) or to refine (harmless exposure to nonculprit beta-lactams, excluding monobactams or carbapenems found) the BLAL accordingly. The note will include a summary of the algorithm’s findings, a suggestion for review of the label in consultation with the patient, a reference to the in-house delabeling procedure (written and video), and contact details for questions and additional information. If the BLAL is not changed in the following 24‐72 hours, the treating physician will be contacted by phone to discuss potential delabeling; reasons to discard the advice will be noted in the electronic case report form (as part of the process evaluation) and in the formal study report (cf. Infra). A distinction is made between definite tolerated re-exposure and presumed tolerance. The former is scored in case of documented administration through the electronic prescribing module (in which prescription and registered administration are required), in the EPR, and/or when bedside uneventful re-exposure could be orally confirmed by the treating hospital physician. The latter is scored when free-text notes or ambulatory prescriptions of antibiotic delivery are identified in the EPR, in the absence of EPR-registered bedside verification by the treating hospital physician.

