### Sample Size Determination

The main aim of our study is to establish the assumed superiority of using the AFC over SOC in increasing the proportion of patients with first-line antibiotics prescribed. Therefore, we look at the proportion of patients receiving first-line or narrow-spectrum beta-lactam antibiotics within the total number of patients receiving antibiotics. The crossover design accounts for seasonal as well as intra- and interhospital differences in overall antibiotic use. Nevertheless, overall antibiotic use will be monitored at the participating sites during this trial’s period.

The following assumptions were applied.

For the control arm, in a recent retrospective study in UZ Leuven, involving 21,999 patients with pneumonia, pyelonephritis, infections associated with heart, kidney, liver, or lung transplantation; appendectomy; coronary artery bypass grafting; and total knee or hip replacement, we investigated the difference in antibiotic use between patients with and without BLAL [21]. It showed that 10.5% of patients with a BLAL received amoxicillin despite their label. Based on the latter, we estimate that 10% of the patients in the control group already receive first-line antibiotics. We add a 5% increase due to indirect learning of our protocol because we cannot exclude that treating physicians learn to use discordances in the medical file for delabeling or refinement of the allergy labels, independent of our study and AFC tool. Considering around 30% of hospitalized patients receive antibiotics during their stay [34], this brings the percentage down to 4.6% in the control group.

For the intervention arm, we previously showed that our CDS approach has the potential to delabel 38% of BLALs [30]. We add a margin of 5% for physicians or patients who refuse to delabel or be delabeled [9]. Considering around 30% of hospitalized patients will receive antibiotics during their stay, this results in an overall estimate for the intervention group of 9.9%.

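### The exploratory implementation analysis pools patients who never received a recommendation with those whose recommendation was not followed, so its contrast mixes the effect of acting on advice with selection by flag status

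*Protocol article*

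**What the plan says.** The protocol article, Statistical Analysis, sets the population: "we will perform an exploratory implementation analysis within the AFC phase". It then closes the classification: "Patients will be classified as with implementation if the BLAL was delabeled or refined after the AFC recommendation, and as not with implementation if otherwise". Scores on the primary endpoint up to day 100 are to be summarized by this status. Any between-group comparison is to be descriptive and read with caution, because implementation arises after allocation and may be confounded.

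Who receives a recommendation is set under BLAL Adjustment. For labels judged wrong, "In case of an incorrect BLAL, a suggestion will be sent to the treating physicians in the EPR". For the rest, "In the case of a correct or undetermined BLAL, no action will be taken". Nothing in the article limits the implementation analysis to patients for whom advice was sent.

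**The concern.** The article motivates the analysis by mechanism: the AFC is expected to change prescribing mainly through label change. A reader will therefore take the split as showing what happens when advice is acted on compared with when it is not. As worded, the second group also takes in every AFC-phase patient for whom there was no advice to act on.

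These patients differ from implementers on what the tool looks for. Under AFC CDS Tool, a label is called incorrect after an uneventful re-exposure, a negative rechallenge or a clearly nonallergic reaction. Unflagged patients include those with an observed allergic reaction or a positive test. The outcome is use of first-line or narrow-spectrum beta-lactams. Flagged patients, most of whom have already had a beta-lactam uneventfully since the label was registered, may receive more of these drugs whether or not the label is changed. At stake is how one exploratory result is interpreted.

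**Working it through.** **Inputs from the protocol article**
- Delabeling share used for planning, and delabel-or-refine share: "38% of BLALs could be delabeled, and another 27% could be refined" (Introduction). This gives 38%, and 38% + 27% = 65%. Both come from the pilot, which also used clinical history and primary care contact.
- Yield of the tool in the proof-of-concept study: "identifying nearly 10% of alleged penicillin-allergic patients" (Introduction). That study covered penicillin labels only.
- Refusal: "We add a margin of 5% for physicians or patients who refuse to delabel or be delabeled" (Sample Size Determination).
- Antibiotic use and planned rate: "Considering around 30% of hospitalized patients will receive antibiotics during their stay, this results in an overall estimate for the intervention group of 9.9" per cent (Sample Size Determination).
- Total inclusions: 3285.

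**Step 1. Reproduce the planned rate.** (0.38 − 0.05) × 0.30 = 0.099, which matches the stated 9.9%. Reading the 5% as relative gives 0.38 × 0.95 × 0.30 = 0.108, which does not match. The planning split is therefore 33% flagged and acted on, 5% flagged and declined, and 62% not flagged.

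**Step 2. Composition of the not-implemented group.** With f the flagged share and a the share flagged and acted on, the proportion of that group that never had a recommendation is (1 − f)/(1 − a). At planning values this is 0.62/0.67 = 92.5%; the other 7.5% is declined advice.

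| Flagged share f | Refusal 5 points (a = f − 0.05) | Refusal 5% relative (a = 0.95f) | Half followed, assumed (a = 0.5f) |
|---|---|---|---|
| 10% | 94.7% | 99.4% | 94.7% |
| 38% | 92.5% | 97.0% | 76.5% |
| 65% | 87.5% | 91.5% | 51.9% |

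**Step 3. What the contrast estimates.** Let q_f and q_u be the concordance of flagged and unflagged patients without any label change, d the effect of acting on advice, and w = 0.62/0.67 = 0.925. Assume that acted-on and declined patients share the same q_f. The contrast is then

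(q_f + d) − [w·q_u + (1 − w)·q_f] = d + w·(q_f − q_u).

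The documents give neither q_f nor q_u, so the following rates are assumptions for illustration only:
- q_f = 30%, q_u = 15%, d = 0: contrast 13.9 points, true effect 0.
- q_f = q_u = 15%, d = 15 points: contrast 15 points, equal to the true effect.
- q_f = 30%, q_u = 15%, d = 15 points: contrast 28.9 points, true effect 15.

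At the planning split, a difference q_f − q_u of 0, 5, 10 or 15 points adds 0, 4.6, 9.3 or 13.9 points.

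**Step 4. Numbers if the groups are separated.** Assume half of the 3285 are in the AFC phase and 30% receive antibiotics: 3285/2 × 0.30 ≈ 493 patients with a defined score. At the planning split this gives about 163 implemented, 25 declined and 306 without a recommendation. At a 10% flagged share it gives about 47 versus 2 (relative refusal) to 25 versus 25 (5-point refusal), with about 443 unflagged.

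**The case against.** The strongest reply is that the article already treats this analysis with restraint. It is exploratory, no causal claim is attached, and the stated caveat about confounding covers the mechanism in general terms. Changed versus unchanged label is a coherent descriptive split, and a patient whose label did not change is truly not implemented. Uptake of advice is also addressed elsewhere: reasons for discarding it are recorded for the process evaluation, and the delabeling or refinement rate is a secondary endpoint. An SAP is still to come, and the wording could be read as presupposing that a recommendation was made.

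Much of this stands, and it rules out several stronger readings that a reader might infer.
- That the contrast is purely flagged versus unflagged and uninformative about acting on advice. Declined patients are in the comparator, about 7.5% of it at planning values and up to 48% in the table above. The contrast would also recover the true effect if flagged and unflagged patients were otherwise alike.
- That it will show a large benefit even if acting on advice does nothing. This needs concordance rates by flag status, which the documents do not give.
- That this is misclassification outside the article's caveat. The mechanism is a form of the confounding the caveat names.
- That every implementer has a documented uneventful re-exposure by definition. A clearly nonallergic reaction also makes a label incorrect under AFC CDS Tool, although BLAL Adjustment ties the delabel and refine suggestions to exposure.

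The wording of the rule remains. The article fixes population and classification explicitly and without restriction, so this is more than detail left to the SAP. The caveat neither discloses that most of the comparator had nothing to implement nor separates those patients.

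**Conclusion.** The point holds as one of low severity. The rule pools patients without a recommendation with patients whose recommendation was not followed, and the former are about 92.5% of the group on the article's own planning figures. The range is about 88% to 99% across flagged shares of 10% to 65% with the planned refusal, and 52% to 95% if half the advice were ignored.

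These shares carry three assumptions. The flagged share among antibiotic-treated patients is taken to equal the share overall. The 10% yield, from penicillin labels only, is taken as a lower value for all beta-lactam labels. The pilot's 38% and 65% are taken as possible yields of the tool, although the pilot used further sources of information. The direction of any bias is plausibly toward a larger apparent benefit; its size cannot be stated from the documents. Only this one exploratory analysis is affected.

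**What to change.** Replace the two-way split with three groups: recommendation made and implemented; recommendation made and not implemented; no recommendation (correct or undetermined label). Summarize the score in all three, and compare implemented with not implemented only among patients with a recommendation. Keep the statement that the comparison is descriptive and confounded, since physicians who decline advice may do so for reasons related to prescribing.

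The cost is one sentence in the SAP, which is to be finalized before a database lock expected in late 2026. No new data appear to be needed: the suggestion is a note in the patient record, and reasons for discarding it go into the eCRF. The downside is precision. At planning values the comparison rests on about 25 declined against 163 implemented patients, and at a low flag rate with few refusals it could rest on a handful. Report the group sizes alongside the estimate.
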